**Methods:**

The study is designed as a multi-center, randomized controlled trial. In total, an estimated number of *n* = 1,500 C&A with mental health problems, drawn from a school-based sample of *n* = 15,000 pupils attending school grades 6 to 13 (≥ 12 years of age), recruited in five regions of Germany, will be randomized either to an intervention (ProHEAD online) or a control condition. C&A in the intervention group will receive online access to tailored information and individual advice on where to seek professional help for their specific needs close to their place of living, case reports of and interaction with peers, as well as the opportunity for online and telephone counseling. C&A in the control intervention will receive a recommendation to seek help and online information on where to find professional help. All participants will be asked to complete questionnaires concerning their help-seeking behavior at baseline, during the intervention (monitoring), and also at a 1 and 2 year follow-up. The primary endpoint is the number of C&A seeking conventional face-to-face professional help in the real-world setting within 1 year after their initial screening.

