By combining these features, interventions based on e-technology might present an effective approach to overcome barriers of help-seeking and to facilitate access to conventional care. Over the past decade, technology has played an increasingly bigger role in the delivery of psychosocial and psychotherapeutic interventions (“e-mental health”). E-mental health and Internet-based interventions have the advantage of easy, low-threshold access, enhanced reach, including traditionally underserved populations, relatively low cost, and time efficiency. In addition, technology allows for providing flexible interventions that are tailored to the individual needs and preferences of participants. Across the spectrum of mental health problems, growing evidence points to the potential of e-interventions for prevention, self-help treatment, counseling, and relapse prevention, and also as an adjunct to conventional psychotherapy using various forms of media and technology [17, 18]. It is assumed that Internet-based interventions may improve mental health literacy and contribute to a de-stigmatization of mental illness, thus promoting help-seeking attitudes, intentions, and ultimately behaviors [19]. However, only a few studies attempted to utilize Internet-based interventions to promote mental help-seeking. A recent review identified 18 studies, all with major methodological limitations (i.e., small sample sizes, lack of control group, no follow-up, and failure to assess behavioral outcomes) [20]. Furthermore, existing Internet-based interventions mostly address one particular health condition (mainly depression or anxiety), rather than providing different modules for a broad range of mental health problems prevalent in C&A all integrated in one superordinate program. Promoting Help-seeking using E-technology for ADolescents (ProHEAD) is such a superordinate program, which covers mental health problems (i.e., conduct problems, hyperactivity/inattention, peer relationship problems, emotional problems, eating disorders, addiction, and suicidality) not jointly covered by other programs. Finally, previous research is limited by the fact that the interventions aiming to improve help-seeking have almost exclusively consisted of one-time, fully automated tools (mostly psychoeducational content), not giving consideration to the heterogeneous and complex pathways to care [15]. By specifically addressing these methodological issues, an intervention based on e-technology bears great potential to conquer various barriers of help-seeking in C&A, to facilitate service access, and to finally contribute to relieve the burden of mental disease in youths.

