### Data assessment

In addition to sociodemographic information (i.e., migration status, socioeconomic status), the school-based screening will cover screening instruments for a broad range of mental health problems. All measures have previously been used in adolescent samples [28–30]. Three self-report instruments will be used to cover help-seeking intentions, actual help-seeking behavior, and attitudes toward help-seeking. The General Help-Seeking Questionnaire (GHSQ [28]) is a self-report measure of help-seeking intentions. Help-seeking intentions for selected mental health problems are assessed on an 8-point scale ranging from 1 (extremely unlikely) to 8 (extremely likely). The Actual Help-Seeking Questionnaire (AHSQ) [31] assesses actual help-seeking behavior by listing potential sources of help and measuring whether or not help has been sought from the respective sources within a specified time period (in the last 12 months; more than 12 months ago). It comprises three sub-scales: whether or not informal help has been sought, whether or not formal help has been sought, and whether no help has been sought. Further, the Inventory of Attitudes Toward Seeking Mental Health Services (IASMHS) [32] will be used. The IASMHS is a 24-item scale and has three internally consistent factors: *psychological openness*, *help-seeking propensity*, and *indifference to stigma*. To assess barriers of help-seeking, 12 items were generated based on a literature review of help-seeking barriers and compared with the validated instrument Barriers to Adolescents Seeking Help Scale (BASH-B [33]). Further, items from the Questionnaire on Social Distance [34], assessing stigma towards peers affected by mental health problems, will be implemented in the screening. Health care utilization of study subjects will be collected by the *Mannheimer Modul Ressourcenverbrauch* (MRV), a scale that lists all possible health care services for a given study sample or risk group and reports the frequency of usage (visits, drug intake, hospital days, etc.) over a given period of time [35]. Similar scales are applied in international cost studies [36]. The MRV was modified and pretested for its use in an adolescent population.

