### Statistical analysis

The main hypothesis is that a greater proportion of those C&A with mental health problems who are randomized to ProHEAD online (intention-to-treat) will present themselves within the conventional professional mental health care system after 1 year compared to C&A in the control condition. This will be addressed using chi-squared tests with Fisher’s exact *F* to adjust for zero inflation of cell distribution sizes (C&A who utilized professional help versus C&A who did not utilize professional help) on group differences. In secondary analyses, predictors of help-seeking behavior (i.e., sex, age, utilization of the online intervention, and symptom severity at initial school-based screening) will be assessed using multinomial logistic regression analyses. Engagement time per participant (minutes per day, days per month) and content of engagement will be tracked to get a reliable estimate of the utilization of the platform that is of interest for analyses of the dose-response relationship. Missing data and subjects withdrawn from the trial will be handled using an intention-to-treat approach. All subjects randomized will be considered in the analyses. In the case of drop-outs or missing data, it will be assumed that these C&A did not present themselves within the mental health care system to provide a conservative estimate of the true effect. Potential class and school effects will be tested and adjusted for if necessary.

In addition, a cost-effectiveness analysis, including the calculation of the incremental cost-effectiveness ratio (ICER), will be conducted. To provide information on cost per quality-adjusted life year (QALY), cost-utility analyses will be used.

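### The secondary predictor model does not name prior formal help-seeking, so the coefficients for severity, age and sex could partly reflect care that was already running at baseline

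*Protocol article*

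**What the plan says.** The Statistical analysis section plans a secondary analysis of "predictors of help-seeking behavior (i.e., sex, age, utilization of the online intervention, and symptom severity at initial school-based screening"; these "will be assessed using multinomial logistic regression analyses". No other section adds a predictor. The only further terms mentioned are possible class and school effects.

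The trial does collect prior help-seeking. The abstract's Methods paragraph says "All participants will be asked to complete questionnaires concerning their help-seeking behavior at baseline" and at later points. The Data assessment section describes the AHSQ as recording whether help was sought from each source "within a specified time period (in the last 12 months; more than 12 months ago", with a sub-scale for formal help.

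Three further statements matter:

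- Inclusion and exclusion criteria: the only stated exclusion is lack of written consent. Nothing excludes a pupil who is already in treatment.
- Outcomes: other treatments are permitted during the trial.
- Outcomes: the primary outcome is actual help-seeking over the past year, without restriction to first or new contacts.

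**The concern.** A pupil in psychotherapy at screening who simply continues can count as a help-seeker at one year. If more severely affected, older or female pupils are more often in care at baseline, and care tends to carry on, then severity, age and sex will be associated with the outcome through that route alone. The named model has no term that separates this carry-over from newly sought help.

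The interpretation of a reported secondary result is at stake. The trial exists to bring untreated pupils into care, so readers will take a predictor of help-seeking as information on who newly seeks help. As specified, the coefficients mix new and continuing contact in unknown proportion, although the variable needed to separate them is already measured.

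**Working it through.** The documents state no figure for this model, so there is nothing to reproduce. The check asks whether the mechanism can operate under the plan's own rules, and how large it could be.

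**Inputs from the documents.** Randomised number 1,500 (Sample size). Share of affected adolescents receiving appropriate professional treatment 25% (Background), used here only as one scenario for the share in care at baseline.

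**Assumptions.** The documents do not give the odds ratio linking severity to prior care (g, per SD), or the one-year help rates for pupils with prior care (p1) and without it (p0). All three are assumed. Severity is given no direct effect on the outcome, so its true odds ratio conditional on prior care is 1.00.

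**Hand calculation.** Let c be the share in care. The help rate is c × p1 + (1 − c) × p0. Take c = 0.25, p1 = 0.70, p0 = 0.15, g = 1.5.

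- At average severity: 0.25 × 0.70 + 0.75 × 0.15 = 0.2875; odds 0.2875/0.7125 = 0.4035.
- One SD higher: odds of being in care (0.25/0.75) × 1.5 = 0.50, so c = 1/3. Help rate 1/3 × 0.70 + 2/3 × 0.15 = 0.3333; odds 0.50.
- Apparent severity odds ratio: 0.50/0.4035 = 1.24 per SD, against a conditional value of 1.00.
- With g = 1.0 the share in care does not move, and the odds ratio is 1.00.

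**Simulation at n = 1,500.** Binary logistic regression (a simplification of the multinomial model) with severity, sex and age, 200 replicates per scenario, p0 = 0.15:

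| In care | g per SD | p1 | Severity OR without prior care | p < 0.05 | Severity OR with prior care | p < 0.05 |
|---|---|---|---|---|---|---|
| 10% | 1.5 | 0.50 | 1.09 | 26% | 1.00 | 5.5% |
| 10% | 2.0 | 0.70 | 1.23 | 89.5% | 1.00 | 2% |
| 25% | 1.0 | 0.70 | 0.99 | 5.5% | 0.99 | 6% |
| 25% | 1.5 | 0.70 | 1.23 | 93% | 1.01 | 7% |
| 25% | 2.0 | 0.85 | 1.48 | 100% | 1.00 | 3.5% |

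Over the whole grid with g of 1.5 or 2.0, 10 or 25% in care, and p1 of 0.50, 0.70 or 0.85, the odds ratio without prior care runs from 1.09 to 1.48 and is significant in 26 to 100% of runs. With prior care it is 0.99 to 1.01.

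**Second set of assumptions.** With 25% in care, g of 1.5 to 2.5, and p1/p0 of 70/10, 60/13.3 or 50/16.7%, large-sample simulation of a model with severity alone gives 1.14 to about 1.65 per SD. Adding prior care again gives about 1.0.

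**The case against.** **Prediction is not causation.** The plan speaks of predictors, and its outcome is any help-seeking in the past year. If severe pupils use more care, partly because their care continues, then severity does predict that outcome. This stands: the marginal coefficient is a valid answer to the question as literally put. What it cannot show is who newly seeks help.

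**The magnitude is built in.** Severity is denied a direct effect, and an assumed link to prior care then produces the association. This also stands. The figures show what could happen, not what will.

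**The list may not be closed.** The article uses the same abbreviation loosely elsewhere, for instance for sociodemographic data, and an unseen analysis plan could add covariates. That limits how firmly one can speak of a closed list. It does not remove the point, because the article does name a list and prior help-seeking is not on it.

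**A stronger reading.** A reader might infer that leaving out the other baseline measures is an equal fault, since the plan also says "Three self-report instruments will be used to cover help-seeking intentions, actual help-seeking behavior, and attitudes toward help-seeking" and "To assess barriers of help-seeking, 12 items were generated based on a literature review of help-seeking barriers", and collects stigma items. The documents do not support that. Leaving these out loses explanatory information but does not create the carry-over problem. The Background also describes e-interventions as expected to "contribute to a de-stigmatization of mental illness, thus promoting help-seeking attitudes, intentions, and ultimately behaviors", so attitudes and intentions may lie on the path to the outcome. Severity, age and sex coefficients taken only from a model holding all of these would be net of likely mediators.

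**Conclusion.** The point holds in a limited form. The stated eligibility, the permitted treatments and the outcome definition together let continuing care count as the outcome. The named model has no prior-care term, and the trial already records what is needed. Coefficients for severity, age or sex could therefore partly reflect continuing care.

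The size is not known from the documents. Under the assumed links, an apparent severity odds ratio of about 1.1 to 1.65 per SD arises with no direct effect; without a link between severity and prior care there is no distortion. Nothing was simulated for age or sex, for which the argument is by analogy.

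Two further inferences should be resisted. The documents do not show that severity will be falsely reported as a predictor, because that depends on the unquantified link. Nor is the randomised comparison of the arms affected: this is a secondary model, and the primary test is not biased by what it omits.

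**What to change.** In the Statistical analysis section, keep sex, age, utilization and baseline severity as stated predictors, and add randomised arm and baseline AHSQ formal help in the past 12 months. Report the severity, age and sex coefficients with and without the prior-help term, so that readers see both the marginal and the conditional association. Alternatively, also report the model in pupils not in care at baseline.

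Keep utilization for the dose-response analysis that the section already plans. Intention, attitude, barrier and stigma scores are optional. If they are used, put them in a separate, further model, because they may be mediators.

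The cost is about one sentence and one extra term for prior help, with no new data collection. The adjusted coefficients must be labelled as conditional on prior care and not read as total associations.

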#### Monitoring Module

A monitoring system allows for the gathering of information regarding the help-seeking behavior of C&A in the intervention group. This will enable the case managers to tailor the intervention to a participants´ individual status, situation, and needs, allowing for adequate and tailored support of C&A. We distinguish automatized monitoring from individual monitoring. Automatized monitoring occurs based on user-website interaction in terms of 15 regular online assessments (Monitoring 1: 7 days after registration; Monitoring 2–7: every 14 days for the following 10 weeks; Monitoring 8–14: every 28 days for the following 32 weeks; Monitoring 15: 301 days after registration). As part of the automatized monitoring, C&A receive emails inviting them to complete a short questionnaire and motivating them to stay engaged with the platform. Automatized monitoring ends if C&A report successful help-seeking within the professional mental health care system. Alongside automated prompts, individual monitoring is realized via a team of case managers; each case manager tracks the progress of particular C&A. The case managers have different occupational backgrounds (e.g., psychologist, health education professional) and are trained in motivational interviewing [37] and all study-specific procedures (i.e., administration of the program). Individual monitoring includes individual communication (chat, phone, and email) regarding the progress and status on a regular basis. After registration participants will have access for up to 10 months. The dose of the intervention is primarily determined by the participating C&A. C&A are free to log in to the web-based platform according to their needs and interest. The system will send automated reminders to C&A who stay absent of the platform and have not made efforts to seek conventional face-to-face professional help.

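### Platform use is entered as a predictor of help-seeking although help-seeking itself changes platform use, so the secondary dose-response estimate is biased in a direction the plan does not fix

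*Protocol article*

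**What the plan says.** The Statistical analysis section of the protocol article introduces the secondary work with "In secondary analyses, predictors of help-seeking behavior". The predictors listed are sex, age, "utilization of the online intervention, and symptom severity at initial school-based screening) will be assessed using multinomial logistic regression analyses". Study arm is not in the list. The same section says that "Engagement time per participant (minutes per day, days per month) and content of engagement will be tracked", in order to obtain a "reliable estimate of the utilization of the platform that is of interest for analyses of the dose-response relationship". It also says that every randomised pupil is considered in the analyses and that a missing outcome counts as no help sought.

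Two rules under Monitoring Module bear on the exposure. The first is "Automatized monitoring ends if C&A report successful help-seeking within the professional mental health care system". The second is "The system will send automated reminders to C&A who stay absent of the platform and have not made efforts to seek conventional face-to-face professional help". That section also gives access for up to 10 months after registration, allows log-in at will, and leaves the dose mainly to the pupil. Under Intervention, the three additional modules are open to the intervention group only.

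**The concern.** Sex, age and baseline severity are fixed before randomisation. Platform use is not, and the intervention's own rules make part of it a result of the outcome. A pupil who reports help-seeking early receives no further automated assessments, while one who does not goes on being invited and, if absent, reminded. Time at risk and opportunity to accumulate engagement are thus tied together.

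Pooling adds a second problem. Controls cannot use the intervention modules, so a two-arm model without an arm term lets platform use carry any difference between the arms.

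At stake is the reading of the dose-response result. An association produced by the stopping rule, or by motivated pupils both engaging more and seeking help, could be taken as evidence on how intensive the programme should be.

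**Working it through.** The article gives no figure for this analysis, so there is nothing to reproduce. The check asks what the planned regression returns when engagement truly has no effect.

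**Step 1: opportunity.** Taking the stated intervals from registration, the 15 automated assessments fall on days 7, 21, 35, 49, 63, 77, 91, 119, 147, 175, 203, 231, 259, 287 and 301, which sum to 2,065. Assume seekers seek help uniformly over 365 days and report it at once. The expected number of assessments offered to a seeker is Σ(1 − d/365) = 15 − 2,065/365 = 9.3, against 15 for a non-seeker. With average completion of one half, unrelated to the outcome, that is 4.7 against 7.5 completed.

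**Step 2: effect on a count.** Assumptions: 750 intervention pupils (1,500 with 1:1 allocation, a ratio the article does not state), 28% seeking help, completion varying between pupils as Beta(2,2), 300 runs. Logistic regression of help-seeking on the number completed gives an odds ratio (OR) of 0.81 per assessment, significantly negative in every run. It stays at 0.80 to 0.81 for help-seeking rates from 10% to 40%. If only half of seekers report, the OR is 0.90 to 0.91, significantly negative in 88% to 99.5% of runs. If the exposure is instead the proportion completed of those offered before help-seeking, the OR is about 1.00, with false positives near the nominal level.

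**Step 3: other metrics, confounding and missing outcomes.** Assumptions: 750 pupils, exponential time to help-seeking, 25% seeking within 12 months, log-engagement SD 0.7, and a shared motivation factor (0 to 0.75 log units per SD) acting on both engagement and help-seeking. There were 100 runs per scenario, tested at two-sided 5%. The table gives ORs per SD of engagement under no true effect, with no missing data.

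| Exposure | Motivation 0 | Motivation 0.5 | Motivation 0.75 |
|---|---|---|---|
| Completed automated assessments | 0.33 | 0.45 | 0.56 |
| Total use, stops at help-seeking | 0.34 | 0.53 | 0.73 |
| Total use, continues at 50% | 0.67 | 1.00 | 1.36 |
| Total use, continues unchanged | 1.00 | 1.40 | 1.82 |
| Rate before help-seeking only | 1.00 | 1.40 | 1.87 |

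Counting 20% missing outcomes, concentrated in low engagers, as no help sought moves the estimates upward. With no motivation effect, 0.67 becomes 0.76, and 1.00 becomes 1.10 in the last two rows. The highest value reached is 2.08 (total use unchanged, motivation 0.75).

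**Step 4: does a rate solve it?** Only with the right denominator. Dividing total use by a common access period, say 301 days, rescales every pupil by the same constant and leaves the OR per SD unchanged. A rate over time before help-seeking removes the artefact (OR 1.00 without confounding). The article does not say which is meant.

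**The case against.** The strongest reply is that the plan names engagement time as rates, not a count of questionnaires. Only automated monitoring is said to end, and only on a report of help-seeking. Individual contact with case managers has no stated stop, and log-in stays open. Step 3 bears this out: if use continues unchanged and nothing confounds it, there is no artefact.

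This disposes of a stronger reading that a reader might infer, namely that the analysis is bound to show more engagement going with less help-seeking. The documents do not support it. The strongly negative result belongs to counts or totals that stop at help-seeking, while a self-chosen dose and the missing-outcome rule push the other way.

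A reader might also infer that a multinomial model is wrong for a binary endpoint. It is not: with two categories it is binary logistic regression, and informal, formal and no help could be coded as exclusive levels.

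It can further be said that an article leaves exposure windows to the full plan, and that time-stamped access logs (Data monitoring and safety) keep a time-limited exposure possible. That is fair as far as detail goes. But the article itself names the exposure, the outcome and the model, places the exposure beside baseline variables, and describes intervention rules that make it depend on the outcome. Followed as written, the analysis is biased. The objection narrows the point without removing it.

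**Conclusion.** The point holds for the secondary predictor and dose-response analyses. Platform use is partly a consequence of help-seeking, and the stated analysis does not separate the two. Under no true effect the OR per SD ran from about 0.33 to about 2.1 over the scenarios examined. That range rests on assumptions the article does not supply: the help-seeking rate, the spread of engagement, use after help-seeking, the strength of motivation, and the pattern of missing outcomes. It shows that sign and size are undetermined and does not forecast the result. Whether the arms would be pooled is not stated; if they are, and no arm term is added, the coefficient also mixes dose with allocation. The randomised primary comparison does not use this exposure and is unaffected.

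**What to change.** State the following in the analysis plan:

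- Run dose-response analyses in the intervention arm only.
- Count engagement only before help-seeking. One option is a landmark: engagement in a fixed early window after registration (for example four weeks) as predictor of later help-seeking, among pupils who have not yet reported it. The other is engagement as a time-varying exposure, using the dates of monitoring reports.
- Say how pupils who never activate their account are counted, since they have no registration date.
- In any two-arm predictor model use baseline variables plus arm.
- Label the dose results exploratory and non-causal. Restricting exposure to the time before help-seeking leaves confounding by motivation in place (OR 1.40 at 0.5 and 1.87 at 0.75 in the last row of the table).

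The cost is wording, since logs and monitoring dates are already collected. There are two downsides. Pupils who seek help before the landmark drop out: with 25% seeking help at a constant hazard over the year, 1 − 0.75^(28/365) = 2.2%, about 16 of 750 pupils, or about 9% of the expected seekers. Timing also rests on monitoring reports, because the Actual Help-Seeking Questionnaire gives only 12-month windows. Pupils who do not answer the monitoring have no date, so an early contact they never reported would be counted as a later one.

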## Hypotheses

The primary hypothesis is that a greater proportion of C&A with mental health problems who are randomized (intention-to-treat) to help-seeking assistance through an individualized online based intervention are more likely to actually utilize professional (formal) face-to-face mental health care from a child and adolescent psychiatrist or psychotherapist within 1 year (primary endpoint), compared to a control group receiving information only. Secondary hypotheses are that C&A allocated to the intervention group will score more favorably on measures of mental health problems, health-risk behaviors, and quality of life in the respective follow-up assessments, compared to the control group. Additionally, health economic analyses will be conducted to assess economic aspects of the newly developed intervention.

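### The rule that counts drop-outs as not having sought help is not limited to the arm comparison, and in the predictor and dose-response models it turns predictors of drop-out into predictors of not seeking help

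*Protocol article*

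**What the plan says.** All the relevant text is in one paragraph of the Statistical analysis section of the protocol article, in this order:

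- The primary hypothesis and its chi-squared or Fisher test of help used versus not used, by arm.
- "In secondary analyses, predictors of help-seeking behavior" are to be examined by multinomial logistic regression. The predictors are sex, age, use of the online intervention and symptom severity at the first screening.
- Engagement with the platform is tracked to give a utilization measure "that is of interest for analyses of the dose-response relationship".
- The missing-data rule: "All subjects randomized will be considered in the analyses", followed by "In the case of drop-outs or missing data, it will be assumed that these C&A did not present themselves within the mental health care" system, which is done "to provide a conservative estimate of the true effect".

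No sentence limits the rule to the primary test, and no other rule is given for the predictor or dose-response models.

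**The concern.** The predictor and dose-response analyses are meant to show which pupils go on to seek care and whether more use of the platform goes with more help-seeking. If every missing pupil is entered as not having sought help, these models partly describe who completed follow-up.

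The design gives reasons to expect the named predictors to be related to follow-up:

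- **Age.** Recruitment covers grades 6 to 13 (Setting and recruitment) and the 1-year outcome is collected in a second school-based assessment (Outcomes). Older pupils who have left school by then can be reached only through the emailed link.
- **Platform use.** The dose is largely the participant's choice (Monitoring Module). A pupil who stops responding to the platform's emails may well also miss the follow-up. Coding that pupil as not having sought help builds in a dose-response relationship.

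The error can create an association or shrink a real one, so the justification given for the rule does not carry over to these models.

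**Working it through.** **The plan's own figures.** There is none to reproduce here. The article gives no drop-out rate and no expected help-seeking rate for the trial. The calculation does not use the effect size in the Sample size section.

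**Inputs.**
- n = 1,500 randomized (Sample size), split for illustration into 750 per level of a two-level predictor (assumed).
- True help-seeking p = 25% at both levels, so the true odds ratio is 1.00 (assumed; range 20% to 30%).
- Drop-out d0 and d1 at the two levels (assumed).
- Within a level, drop-outs seek help as often as pupils who are followed up (assumed).
- Two-sided 5% test of two proportions, normal approximation.

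**Formulas.** Under the rule, coded rate = p × (1 − d). The apparent odds ratio is [b/(1 − b)] / [a/(1 − a)], with a = p(1 − d0) and b = p(1 − d1).

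**Results at p = 25%.**

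| Drop-out | Coded rates | Apparent odds ratio | Chance of a significant false effect |
|---|---|---|---|
| 10% v 10% | 22.5% v 22.5% | 1.00 | 5% |
| 10% v 20% | 22.5% v 20.0% | 0.2500 / 0.2903 = 0.86 | about 22% |
| 10% v 30% | 22.5% v 17.5% | 0.2121 / 0.2903 = 0.73 | about 68% |

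For the second row, z = 0.025 / √[(0.225 × 0.775 + 0.20 × 0.80)/750] = 0.025 / 0.0211 = 1.18. For the third, z = 0.05 / √[(0.225 × 0.775 + 0.175 × 0.825)/750] = 0.05 / 0.0206 = 2.43.

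**Range for p from 20% to 30%.** Drop-out of 10% v 20% gives odds ratios of 0.87 to 0.85 and false-effect chances of 18% to 26%. Drop-out of 10% v 30% gives 0.74 to 0.72 and 56% to 78%.

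**Platform use.** Take the intervention arm alone, 375 high and 375 low users (assumed), with no true effect and p = 25%. Follow-up of 90% v 70% gives an odds ratio of 0.73 for low use and a false-effect chance of about 40%.

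**A real effect shrunk.** True help-seeking of 20% at low severity and 30% at high severity is an odds ratio of 0.4286 / 0.2500 = 1.71. With drop-out of 10% and 30%, the coded rates are 18% and 21%, and the odds ratio falls to 0.2658 / 0.2195 = 1.21.

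**Observed pupils only.** Under the same assumptions the rate among pupils followed up is p at each level, so a null predictor stays at 1.00.

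**The case against.** The best reply is that the rule was written for the primary endpoint. Its wording echoes the primary hypothesis, its stated purpose fits an arm effect, and nothing in the article calls it conservative for predictors. That may well be the intention. Even so, the text speaks of the analyses in the plural, comes after the predictor and dose-response analyses in the same paragraph, and excludes none. An analyst following it would apply it there.

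A second reply is that the regression is multinomial, which suggests more than two outcome categories; the Actual Help-Seeking Questionnaire separates informal, formal and no help. This stands as a limit on the figures, which are for an unadjusted two-category outcome. It does not remove the problem. The rule keeps every drop-out out of the formal-help category without saying which other category they join.

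Third, the size depends on assumed drop-out, and the emailed link should recover some pupils who miss the school assessment. This also stands. One can choose an extreme scenario, such as a small group of leavers who are mostly lost, and make a false age effect nearly certain. The documents do not support that as an expected result.

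Two stronger readings are tempting and should not be drawn:

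- **That drop-outs enter the cost analysis with no care.** The cost analysis stands in a separate, later paragraph ("In addition, a cost-effectiveness analysis, including the calculation of the incremental cost-effectiveness ratio (ICER), will be conducted") that does not invoke the rule. Its resource-use instrument records visits, drugs and hospital days, which a yes/no assumption cannot fill.
- **That the plan fails because the rule gives no value for the secondary outcomes** ("measures of mental health problems, health-risk behaviors, and quality of life in the respective follow-up assessments"). This is a gap that a condensed article may leave to the full protocol or analysis plan.

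**Conclusion.** The point holds for the predictor and dose-response models of help-seeking. The rule as written covers them, and there it biases associations in either direction according to how each predictor relates to follow-up. Across the assumed range, a predictor with no effect would show an odds ratio of about 0.72 to 0.87, with a false-effect chance of roughly 18% to 78%. With equal drop-out there is no bias for a null predictor.

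The figures rest on assumed help-seeking and drop-out rates, a binary outcome without covariates, and drop-outs who seek help as often as others at the same predictor level. If drop-outs in truth sought less help, the bias is smaller; if none of them did, the coding would be right.

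These are secondary analyses, and the point leaves the primary conclusion untouched. Whether the rule is in fact conservative between arms is a separate question that this check does not settle.

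**What to change.** 1. State that counting missing pupils as not having sought help applies to the primary arm comparison only.
2. Fit the predictor and dose-response models on multiply imputed data. The imputation model should include arm, region, grade, sex, age, baseline scores, baseline help-seeking and platform use.
3. Report the same models in observed pupils as a check.
4. State the outcome categories of the multinomial model, so that the handling of a missing pupil is defined.

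The cost is a few lines of analysis-plan wording and routine imputation work; design and data collection do not change. The downside is that imputation assumes data are missing at random given the collected variables, and the plan should say so.
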